### 3.5. Data Collection

We will use qualitative methods including FGDs, KIIs and DOs to gather detailed information on maternal and child nutrition practices, and the influence of local cultural beliefs related to these practices. All the focus group discussions and interviews will be audio recorded after obtaining oral consent from the participants. The field researchers will use an observation guide to perform their DO work. While observing, the researchers will take notes of key things that they see. Once the observation is finished, the field researchers will immediately write expanded notes of their observations and write a report. DOs will be carried out in the households of PLW. Each of these observations will focus on the preparation and eating habits of most common food recipes for PLW and children aged 6–24 months throughout the day and on interactions between family members. In the field notes, the field researchers will write their own reflections and impressions of the information they collected through the KIIs, FGD and DO. The core study team members (study coordinator and study manager) will supervise the data collection during practice and during the data collection. Supervision will be carried out by reading the transcripts line-by-line and giving detailed feedback on each transcript from KII, FGD, as well as the DO reports. The study investigators will have close communication with the field researchers by email, other messaging systems and by Skype meetings.

Baseline and endline data will be collected on paper forms and then will be entered on tablets. A customized application will be developed using Java on SQLite backend for data storage. The key features of the data collection application will include access control, onscreen consistency and range checks, onscreen tips and quick reports. Range and consistency checks as well as skip patterns will be built into the program to minimize the entry of erroneous data. Special arrangements will be made to enforce the referential integrity of the database to ensure that all data tables are related to each other.

Two trained staff will measure anthropometric measurements. The first measurer will measure and record each anthropometric measurement without revealing the values obtained to the second measurer. The second measurer will then independently repeat the same measurements. Each measurer will record their own values independently with no knowledge of the values recorded by the other measurer. After collecting the data, the two measurers will compare their measurements to ensure that the differences between their measurements fall within the standard maximum allowed differences (7 mm for length and 50 g for weight). Any pair of measurements falling outside the maximum allowed differences will be repeated by both measurers and will be entered on the recording sheet. If this second pair of measurement values again exceed the standard limits for that measurement, the measurers will repeat the measurement for a third and final time.

Mother and child weight will be assessed using a calibrated balance allowing double weighing (mother–child) and an automatic deduction of the mother’s weight to obtain the child’s weight. An SECA brand weight machine will be used for weight measurement with an accuracy of 50 g. The children’s length will be measured using an SECA length board with an accuracy of 0·1 cm. Mother and child hemoglobin levels will be tested using HemoCue Hb 201 analyzers.

At the endline survey, mothers will be asked about the exposure to specific components of the intervention package, such as familiarity with their health facility, CHWs, participation in individual and group counseling sessions and awareness of SBCC messages on maternal diet and IYCF. Maternal dietary diversity will be assessed by Minimum Dietary Diversity for Women and IYCF practices using the WHO IYCF module. Extensive information will also be collected on the use of supplements, including how it was consumed (mixed or eaten alone), if the mother and child liked the Super Cereal and LNS, any changes (both positive and negative) since the mother and child started consuming these supplements and how many monthly batches had been collected from the nearest health facility or from mobile teams or CHWs. The mothers’ reported recall along with supplements’ distribution data will be collected to assess the compliance of supplements.

### 3.6. Programme Monitoring, Evaluation and Learning

Program monitoring data will be collected on a monthly basis for process evaluation and learning. The expected utility of this process of monitoring data will be to assess the distribution of supplements, the number of mother groups formed, the key SBCC messages delivered, food demonstrations, the development of local recipes, monthly mother group meetings, CHW meetings held on various SBCC activities and the identification of model families. The data will be collected through monitoring the checklists from study participants, program staff and key stakeholders related to the delivery of the intervention.

### 3.7. Data Analysis Plan

The qualitative data will be analyzed using Framework Analysis developed by Ritchie and Spencer in 1994 [43]. Since the current formative research has specific questions related to food habits and IYCF practices that will help to design the SBCC strategy. The recordings of FGDs and KIIs will be translated into English and supplemented by field notes and informal observation throughout the fieldwork. Two researchers will read through the transcripts and field notes repeatedly to identify emerging themes and will agree upon a preliminary coding framework. A third researcher will look independently at a subset of transcripts to verify the themes in the original framework and identify additional ones. A coding framework will be agreed, and the remaining transcripts will be read and coded by the two researchers. The framework will use our main topics of interest, nutrition during pregnancy and post-partum, breastfeeding and complementary feeding practices, and sub-themes will be identified within these broader categories. In addition, we will identify important underlying themes related to the socio-economic context, which ran through each of the categories mentioned above.

The baseline and endline analysis will be designed to provide estimates of key indicators at intervention and control levels. Initial analysis will include examining the frequency distribution of all the variables to identify possible errors. The final analyses will be performed after data cleaning and satisfactory quality assurance. Descriptive statistics for the subjects will be estimated and reported as means (±SD), medians, ranges and frequencies as appropriate. The anthropometric measurements, together with the age and gender of the children, will be used to calculate the weight-for-age, height-for-age and weight-for-height z-scores. The prevalence of malnutrition in its different forms (underweight, wasting and stunting) will be calculated using the z-score cut-off point of <2 SD using the WHO growth standards 2006. BMI will be calculated by dividing their weight in kilograms by the square of their height in meters as Underweight (<18.0 kg/m^2^), Normal (18.0–24.9 kg/m^2^), Overweight (25–29.9 kg/m^2^) and Obese (≥30 kg/m^2^. Anemia will be defined as hemoglobin levels <11gm/dl for children aged 6–23 months and <12gm/dL for PLW. All analysis will be performed on Stata version-15.

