### 1.4. Secondary Outcomes

Impact on low birth weight (birth weight < 2500 g) by improving maternal nutrition.Impact on reduction in the prevalence of wasting (WLZ < −2 SD) and underweight (WAZ < −2 SD) in children under two years of age.Improvement in IYCF practices.Improvement in minimum acceptable diet and minimum dietary diversity among PLW.Improvements in care-givers’ knowledge, attitudes and practices related to infant and young child feeding.Improvement in mean hemoglobin concentrations in children and PLW.Improvement in maternal BMI z-scores.Formulation and adoption of local recipes for complementary feeding of children aged 6–23 months using locally available nutritious foods.

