### 3.4. Sample Size for Programme Evaluation Surveys

A total of 2912 children <2 years with their mothers (1456 per group per survey) were estimated to provide reasonable precision (80% power, 95% confidence interval, design effect of 1.5 and response rate of 95%) for baseline and endline surveys based on a 13% reduction in the prevalence of stunting in children under two years old in the intervention areas, as compared in the control areas at endline.

To calculate the sample sizes for anemia (1125 mothers and 810 children per group per survey) with 80% power, a 95% confidence interval, a design effect of 1.5 and a response rate of 95% were estimated to detect a relative 20 and 13% decline in the prevalence of anemia among mothers and in children at endline, respectively.

All pregnant and lactating mothers with children under two years of age will be eligible for baseline and endline surveys. Eligible participants will be identified through two levels.

At health facilities, a list of pregnant women who accessed ANC services and breastfeeding mothers who accessed PNC and childcare services will be prepared.At the community level, a list of PLW and children will be prepared through CHWs. These will include those PLW and children who were not captured at the health facility level.

The baseline and endline surveys will follow a two-stage cluster sampling design. In the first stage, 30 clusters will be randomly selected from each intervention and control area (60 total) using probability proportional to the population size (PPS) sampling design. The data collection teams will prepare a list of all the PLW with children under two years old in each selected cluster and required households from each cluster will be randomly selected for the survey. There will be no replacement in case of refusal. The same sampling design will be used at endline.

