## 4. Results

The primary study finding will be the impact of intervention on the prevalence of stunting among children under two years old in the intervention group compared to the control group. Secondary findings will be the prevalence of low birth weight in newborns and the prevalence of wasting, underweight, anemia and IYCF practices among children under two years of age. Furthermore, we will also report the minimum dietary diversity, anemia and nutritional status among PLW. We will aim to compare the results of the intervention and the control group between the pre- and post-intervention assessments to isolate the effect of the intervention by difference-in-differences estimates.

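### Section 3.7 does not match the declared outcomes on maternal BMI and on the z-score cut-off, and pooling pregnant with lactating women leaves maternal outcomes open to composition bias

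*Protocol article*

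**What the plan says.** **Maternal BMI.** Section 1.4 lists as a secondary outcome "Improvement in maternal BMI z-scores". Section 3.7 says "BMI will be calculated by dividing their weight in kilograms by the square of their height in meters as Underweight" and continues with Normal, Overweight and Obese classes in kg/m². The only z-scores that 3.7 computes are the children's weight-for-age, height-for-age and weight-for-height.

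**Haemoglobin and anaemia.** Section 1.4 declares "Improvement in mean hemoglobin concentrations in children and PLW". Section 3.7 says "Anemia will be defined as hemoglobin levels <11gm/dl for children aged 6–23 months and <12gm/dL for PLW". Section 4 adds that "we will also report the minimum dietary diversity, anemia and nutritional status among PLW", and section 3.4 sizes the anaemia comparison "to detect a relative 20 and 13% decline in the prevalence of anemia among mothers and in children at endline, respectively", with 1125 mothers per group per survey. None of these separates pregnant from lactating women.

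**Design.** Sections 2.1 and 3.4 describe repeated cross-sectional surveys with the same two-stage cluster sampling at baseline and endline. Pregnant and lactating women are eligible and listed together, and no quota or weight for pregnancy status is stated. The effect measure is a difference-in-differences.

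**Child cut-off.** Section 3.7 says that underweight, wasting and stunting "will be calculated using the z-score cut-off point of <2 SD using the WHO growth standards 2006". Sections 1.1, 1.3 and 1.4 place the cut-off below minus 2 SD.

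**The concern.** There are three separate matters, of unequal weight.

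1. The declared BMI outcome and the analysis rule are different quantities. If they are not reconciled, the choice between a z-score, mean BMI and underweight prevalence could be made after the data are seen. BMI is also hard to interpret across a mixed group, because weight in pregnancy includes the pregnancy.

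2. Different women are measured in each round. If haemoglobin or anaemia differs on average between pregnant and lactating women, the pooled figure depends on how many of each are sampled. A shift in that mix in one arm only is not removed by the difference-in-differences. It could create an apparent programme effect or hide a real one. The same applies to mean haemoglobin, although that outcome needs no threshold.

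3. The analysis section governs how stunting, the primary outcome, is coded, and there the sign of the cut-off is missing.

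**Working it through.** **1. BMI, declared outcome against rule.** Section 1.4 needs a maternal z-score. Section 3.7 supplies weight over height squared, four classes, and one reference, the WHO child growth standards, named in the sentence on the children's malnutrition indicators. No maternal reference is given, so the declared quantity does not follow from the stated rule.

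Sensitivity of pooled mean BMI to mix, under assumed values (not in the article) of 5 kg mean pregnancy weight and 1.55 m height:
- Pregnancy adds 5 / 1.55² = 2.08 kg/m².
- A differential shift of 5, 10 or 20 points in pregnant share moves the mean by 2.08 × 0.05 = 0.10, 2.08 × 0.10 = 0.21 or 2.08 × 0.20 = 0.42 kg/m².
- The result is proportional to the assumed weight: each kilogram counts for 1 / 1.55² = 0.42 kg/m² per pregnant woman.

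**2. Anaemia, implied target.** Section 3.4 gives 1125 mothers per group, 80% power, 95% confidence, design effect 1.5, response rate 95% and a 20% relative decline, but no baseline prevalence. Solve for the prevalence p at which the usual two-proportion sample size for p against 0.8p, multiplied by 1.5 and divided by 0.95, equals 1125:

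| p | n per group |
|---|---|
| 0.30 | 1357 |
| 0.34 | 1137 |
| 0.342 | 1128 |
| 0.343 | 1123 |
| 0.35 | 1092 |

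So p is about 0.34, and the target drop is 0.20 × 0.342 = 0.068, or about 6.8 points.

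**3. Anaemia, spurious change from mix.** Let g be the prevalence gap between pregnant and lactating women under the single rule, taken as the same in all arms and rounds. Let s be the change in pregnant share in the intervention arm minus the change in the control arm. With no programme effect, the pooled difference-in-differences shifts by g × s. Both inputs are assumed, since the article gives neither:

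| g \\ s | 5 points | 10 points | 20 points |
|---|---|---|---|
| 5 points | 0.25 | 0.5 | 1.0 |
| 10 points | 0.5 | 1.0 | 2.0 |
| 20 points | 1.0 | 2.0 | 4.0 |

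In percentage points, the range is 0.25 to 4.0. Against 6.8 that is 0.25 / 6.8 = 4% to 4.0 / 6.8 = 59% of the target. If s = 0, the shift is zero whatever g is.

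**4. Cut-off.** In the reference population, P(z < −2) = 2.3% and P(z < +2) = 97.7%. With 45 to 50% of children below −2 SD (1.1 gives above 45% for the intervention districts) and an assumed z-score SD of 1.0 to 1.5, between 99.4% and essentially 100% fall below +2 SD. The printed rule therefore cannot be the intended one. The primary outcome in 1.3, and wasting and underweight in 1.4, carry the correct sign.

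**The case against.** **Haemoglobin and anaemia can be computed as written.** This stands. Mean haemoglobin needs no threshold, and anaemia in PLW follows from the single rule. A reader might infer that 3.7 fails to deliver these outcomes, or that the shared threshold is wrong for pregnant women. The article supports neither: it contains nothing on a different threshold in pregnancy, and that argument would rest on outside guidance. What remains is sensitivity to composition.

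**A stable or equally changing mix cancels.** This also stands: the same rule and sampling design apply in both arms and rounds, so only a differential shift biases the estimate. Such a shift is nevertheless possible. Section 3.4 identifies pregnant women partly from antenatal attendance, and the programme gives pregnant women a monthly ration in the intervention districts only, which could change who is listed there at endline. That is an inference; the article does not report a shift.

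**The BMI sentence does not say whom it covers.** True: the pooled reading comes from the absence of any split and from section 4's nutritional status among PLW. The mismatch with z-scores does not depend on it.

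**Subgroup reporting belongs in the analysis plan.** A statistical analysis plan not shown here may stratify by pregnancy status. The conflict between 1.4 and 3.7, however, lies within the article.

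**The missing sign is trivial.** Largely so. A reader might infer that the primary outcome is undefined or that nearly every child would be counted as stunted. Three other sections give the correct cut-off, no analyst would apply the printed one, and the sign may have been lost in typesetting or text extraction.

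**Conclusion.** The point holds in three limited parts.

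- **Maternal BMI:** a definite mismatch between 1.4 and 3.7. It is resolved by naming the quantity to be analysed, so it would be too strong to say that no maternal BMI outcome can be produced.
- **Pooling of pregnant and lactating women:** an avoidable exposure, not a demonstrated bias. Its size is 0.25 to 4.0 percentage points of anaemia under the assumed gaps and shifts, against about 6.8 points. That target itself rests on the back-calculated baseline of about 34%. For mean BMI it is roughly 0.1 to 0.4 kg/m² under the assumed weight and height.
- **Cut-off sign:** a notation correction. The primary outcome is correctly defined elsewhere.

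The first two affect secondary outcomes only. They deserve correction because the remedy is cheap and best fixed before endline data are seen.

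**What to change.** 1. In 1.4, replace maternal BMI z-scores with mean BMI (kg/m²) and underweight prevalence, and make 3.7 agree. Analyse them in non-pregnant (lactating) women, or separately by pregnancy status. The first option drops a group that the programme targets; the second keeps it visible.
2. For haemoglobin and anaemia, estimate the difference-in-differences separately in pregnant and lactating women. Standardise any pooled figure to one fixed pregnant share, the same in both arms and rounds, and report the observed share for each arm and round. No change of threshold is needed for this.
3. In 3.7, correct the cut-off to z < −2 SD, in line with 1.1, 1.3 and 1.4.

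**Cost.** Items 1 and 3 are wording. Item 2 loses precision within strata: the 1125 mothers were sized as one group, and a stratum holding a share π of them has a standard error larger by roughly 1/√π. The article does not state π, so the loss cannot be quantified here. No new data are needed provided pregnancy status is recorded. That is an assumption, but a reasonable one for a questionnaire that covers antenatal care and the diets of pregnant and lactating women (3.1).

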## 4. Results

The primary study finding will be the impact of intervention on the prevalence of stunting among children under two years old in the intervention group compared to the control group. Secondary findings will be the prevalence of low birth weight in newborns and the prevalence of wasting, underweight, anemia and IYCF practices among children under two years of age. Furthermore, we will also report the minimum dietary diversity, anemia and nutritional status among PLW. We will aim to compare the results of the intervention and the control group between the pre- and post-intervention assessments to isolate the effect of the intervention by difference-in-differences estimates.

## 5. Discussion

To our knowledge, this will be first study to explore the effects of nutritional supplements and SBCC on a reduction in the prevalence of stunting during the first 1000-days of life in Afghanistan. The study findings will be disseminated through workshops held at provincial, country and international levels. The findings from this study will be disseminated via conference presentations and publications in peer-reviewed journals.

The implications of this project are substantial as the program is aimed to prevent stunting through empowering the targeted communities and strengthening their capacity to adopt appropriate IYCF practices; the feedback on progress will be shared with communities through their monthly mother care group sessions. The results generated from the study will be beneficial to design interventions to prevent stunting within Afghanistan and other similar low–middle-income countries.

## 6. Study Strengths and Limitations

The study will be among the first to evaluate the effectiveness of SNF targeting pregnant and lactating women and children aged 6–23 months and SBCC strategies on a reduction in the prevalence of stunting among children in Afghanistan.Program monitoring and evaluation data will allow us to examine the quality of implementation, the acceptability of intervention, the identification of potential barriers and to learn how to enhance the program’s effectiveness through ongoing operational improvements.The cohort of enrolled PLW and children will help to understand the feasibility and adherence to intervention within a community over a 12-month period.The quasi-experimental design limits the choice in the selection of study area and the random selection of health facilities.

## Figures and Tables

**Figure 1 mps-04-00055-f001:**
[figure not shown]
Program theory of process pathways for the intervention package.

**Table 1 mps-04-00055-t001:** Program implementation and SBCC strategy.

Intervention Activities	Frequency	Lead	Implementing Partners	Sources and Mean of Verification
PLW will receive 7.5 kg of super cereal during pregnancy and first 6 months of lactation. Children 6–23 months will receive 30 sachets of LNS-MQ. Anthropometric measurements by AKHS health facility staff.	At enrolment and monthly	WFP, AKU and MoPH	AKHS, AKF 2 Mobile Teams	Recruitment registers Household M&E data Monthly report
Train 80 CHWs on SBCC and intervention activities by AKF.	Once at start of project	WFP, AKU and MoPH	AKF	Training sheet Key SBCC messages Flip charts Monthly report
Train 800 family health action group (FHAG) members in 40 health posts on maternal nutrition, IYCF and key SBCC messages by AKF.	Once at start of project	WFP, AKU and MoPH	AKF	Training sheet Flip charts Key SBCC messages Household M&E data Monthly report
200 SBCC sessions with parents in program villages by AKF (Total 4000 participants/20 per session). SBCC messages delivered by AKHS health facility staff in each visit. SBCC messages delivered by CHWs.	Once at start of project and monthly	WFP, AKU and MoPH	AKF, AKHS	Key SBCC messages Flip charts Household M&E data Monthly report
Train and follow-up of 5000 PLW at community level about the importance of 1000-days, maternal nutrition, IYCF and key SBCC messages (25 PLW/session in program villages).	Once at start of project	WFP, AKU and MoPH	AKF	Key SBCC messages Flip charts Household M&E data Monthly report
200 healthy food preparation and demonstration sessions by AKF in all catchment villages (1 session/village).	Once at start of project	WFP, AKU and MoPH	AKF	Food items and demonstration equipment Key SBCC messages Monthly report
Training for 14 health facility staff of AKHS (2 staff per health facility).	At start and mid of study	WFP, AKU and MoPH	AKHS	Pre-post-test Midterm report

